### Surgical procedure

All participants will have blood tests, including re-measurement of 25-OH vitamin D on the day of surgery, prior to the start of the operation. Patients receiving vitamin D supplementation will also have their calcium level re-checked to monitor for hypercalcaemia. They will undergo primary THR/TKR under the care of their consultant orthopaedic surgeon, and no specific guidance is given with regard to choice of implant, surgical approach, closure, peri-operative care, rehabilitation or clinical follow-up; the approach is pragmatic and should be routine care for that unit.

### Post-operative follow-up

For the purposes of the trial, all participants will be seen again at 6 months following surgery to repeat the diet and lifestyle questionnaire and to re-measure their 25-OH vitamin D level. They will also be reminded about completion of the routine 6-month post-operative PROM scores sent by the NHS. Those participants who were randomised to receive treatment will also be asked to complete an adherence to supplementation questionnaire and return their vitamin D supplement packets.

### Outcomes

The overall aim of this study is to determine if it is feasible to run a large, multi-centre clinical trial to investigate the effect of vitamin D supplementation on outcome following THR/TKR. We will analyse the trial processes, which are key to the future study. We will record the number of eligible patients per site as well as recruitment, retention and refusal rates. The proportion of patients undergoing primary THR/TKR who did not meet the eligibility criteria will also be calculated to ensure that this is not too limiting.

The primary clinical outcome measurement for the trial is the effect of vitamin D on health gain following THR/TKR. Health gain is calculated as the difference between pre-operative and post-operative PROM scores. Condition-specific health gain is measured using either the Oxford hip or knee scores, whilst generic health is measured using the EQ-5D-3 L. We will obtain the routine patient-level PROM data that is supplied to NHS trusts to determine these outcomes.

Secondary outcomes include length of hospital stay, readmission rate and complications. To determine these outcomes, we will interrogate data routinely held in patient records and hospital databases at the study sites. These databases will allow the research team to collect demographic data, co-morbidities, hospital episode statistical data (including length of stay, readmission within 30 days of surgery, return to theatre within 30 days of surgery, requirement for critical care during admission), and complication data to include 30-day medical complications, 60-day thromboembolic complications, 90-day mortality and any superficial or deep infections within the study period. Any expected or unexpected adverse events will be recorded on a trial adverse events form and reported to the sponsor. Any serious adverse events, including death, those prolonging or requiring hospitalisation, causing permanent or significant disability/incapacity, or a life-threatening condition, will be reported to the sponsor and the research ethics committee. The relationship to the study will also be determined. The sponsor has usual NHS indemnity.

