### Trial management

The trial management group is the executive decision-making body and is responsible for the day-to-day running and management of the feasibility study. Led by the chief investigator, it will consist of the lead investigator, research nurses, and statistician. The team will meet on a monthly basis by teleconference and face-to-face at least once per year. It will monitor adherence to the trial protocols at the trial sites. Quality assurance checks will be undertaken to ensure the integrity of randomisation, study entry procedures and data collection. Safety and efficacy will be assessed using adverse event data collection. This will be analysed 6 months from the study opening to recruitment and again at 12 months.

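### Readmission and complication outcomes are sourced from the two study sites' records, and no question about care received elsewhere is described at the 6-month visit, so outside events may be under-counted

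*Protocol article*

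**What the plan says.** The Outcomes section of the protocol article lists length of stay, readmission and complications as secondary outcomes and then gives their source: "To determine these outcomes, we will interrogate data routinely held in patient records and hospital databases at the study sites". The items drawn from that source include "readmission within 30 days of surgery", 30-day medical complications, 60-day thromboembolic complications, and "90-day mortality and any superficial or deep infections within the study period". No general-practice record, other hospital, national linkage or patient report is named for them.

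The same section sets up a separate safety channel: "Any expected or unexpected adverse events will be recorded on a trial adverse events form and reported to the sponsor". Serious events, among them those that require or prolong a hospital stay, go to the sponsor and the ethics committee. The Trial management section adds that "Safety and efficacy will be assessed using adverse event data collection", with analyses 6 and 12 months after the study opens.

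The Post-operative follow-up section has every participant "seen again at 6 months following surgery to repeat the diet and lifestyle questionnaire and to re-measure their 25-OH vitamin D level". It adds a reminder about the routine PROM forms and, for those allocated supplements, an adherence questionnaire and the return of packets. It describes no question about complications or care received elsewhere.

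**The concern.** Several of the listed events need not be treated where the operation was done. A superficial wound infection can be managed in primary care, and a thrombosis or readmission can be handled at another hospital. If the outcome is counted from the operating trust's records, such an event counts only if word of it reaches those records.

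The Background cites peri-prosthetic infection among the problems linked to vitamin D deficiency, so infection is a clinically relevant secondary outcome here. There is also a feasibility question: does a site-record search capture complications well enough to be relied on? With a single stated source, the trial cannot tell how much that source misses. Every participant attends a visit at which this could be asked, but no such question is described.

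**Working it through.** The article states no figure on this point, so the check sets the sections side by side.

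**1. Which outcomes are exposed?**

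| Outcome | Window | Could it be managed outside the two trusts? |
|---|---|---|
| Length of stay, critical care during admission | Index admission | No; the operating site holds the record |
| Readmission, return to theatre | 30 days | Yes, at another hospital |
| Medical complications | 30 days | Yes, in primary care or at another hospital |
| Thromboembolic complications | 60 days | Yes, at another hospital |
| Superficial or deep infection | Study period | Yes; superficial infection especially, in primary care |

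Infection combines the longest window with the setting least likely to leave a hospital record. Even if the hospital episode data mentioned in Outcomes reached beyond the two trusts, they would not show a wound infection treated only in general practice.

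**2. Does another described step close the gap?** The Surgical procedure section leaves clinical follow-up to each unit's routine, so what enters site records after discharge is not standardised. The adverse events form is not limited to events at the sites. However, the article does not say how or when events are elicited for it, or that its contents count towards the secondary outcomes.

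**3. Would a question at 6 months arrive in time to be used?** The Participant recruitment section allows 2 months for recruitment, up to 3 months to surgery and 6 months to the post-operative scores. The last visits therefore fall at about 2 + 3 + 6 = 11 months after opening. Answers would be available for the 12-month adverse event analysis, but not for the 6-month one, since nobody can be 6 months past surgery by then.

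**4. Can the under-count be sized?** Let N be the number of participants, p the proportion with an event, s the share of events managed elsewhere and r the share of those that still reach the site record or the form.

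Missed events = N × p × s × (1 − r)

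Only N = 100 is in the document. Purely as an illustration for infection, assume p from 2% to 10%, s from 25% to 75%, and r = 0 (nothing recovered):

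- low: 100 × 0.02 × 0.25 = 0.5 infections
- high: 100 × 0.10 × 0.75 = 7.5 infections

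The range is wide because every input except N is assumed, and r above zero would lower both ends. The proportional understatement is s × (1 − r), which simply returns the assumption. No percentage can be claimed from the documents.

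**The case against.** The strongest reply is that site records are not the only safety channel. A reader might infer that safety events reach the trial through site records alone. That is not supported: the adverse events form and serious adverse event reporting cover events wherever they occur, and a readmission to another hospital would be reportable. What remains is narrower: the stated source of the secondary outcomes is site records, and the form's link to those outcomes is not stated.

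A reader might also infer that nobody asks about events at 6 months. The article is condensed, and its schedule figure and the case report form are not shown. All that can be said is that no question is described.

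Three further inferences fail.

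- **Reporting that differs by arm.** Treatment is open and only treated patients have the adherence questionnaire and packet return. But the record search is described alike for all groups, so that content cannot bias it. That it prompts more entries on the adverse events form is conjecture.
- **A rate understated by a quarter to a half.** Such a figure only restates an assumed share of events treated elsewhere.
- **A definitive trial planned on these event rates.** The Statistical analysis section lists what feeds the next trial: PROM means and SDs, minimal clinically important differences, retention, recruitment and resources. Event rates are not among them.

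It is also fair to say that routine data are a deliberate, consistent choice in a pragmatic feasibility trial, that event rates in 100 patients would be imprecise however they were collected, and that self-report has weaknesses of its own in an open trial. These points limit the importance of the matter. They do not remove the possible under-count, and the site-record search can stay in place beside the added question.

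**Conclusion.** The point holds in a limited form. As described, the secondary outcomes of readmission and complications rest on the two trusts' own records. The visit that all participants attend has no described question about care elsewhere, and the adverse events form is not tied to these outcomes. Events managed outside the trusts may be under-counted, superficial infection above all.

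The size is unknown. The conclusion assumes only that some such events are treated elsewhere and do not all reach site records. It concerns secondary outcomes in a trial that disclaims direct inference on clinical outcomes, so this is a cheap improvement rather than a fault that threatens the trial's main purpose.

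**What to change.** 1. In Post-operative follow-up, add one short scripted question at the existing 6-month visit, worded identically for all three groups. It should cover wound or joint infection or antibiotics for it, thrombosis, and readmission or further surgery at any hospital.
2. Record the answers on the existing adverse events form and check positive answers against whatever records are available.
3. In Outcomes, state that the form supplements the site-record search for these secondary outcomes.
4. Report how many events each source found. The site-only count is then preserved, and the trial learns what a record search alone would have missed.

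The cost is a few minutes per visit and space on a form already in use. Recall over 6 months is imperfect, and site records may be unable to confirm an event treated elsewhere. Participants who do not attend remain dependent on the record search, and deaths must still be found through records and serious event reporting. If the full protocol already contains such a question, only steps 3 and 4 are needed.

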### Statistical analysis

A secure Excel database (Microsoft Inc., Redmond, WA, USA) will be used to record data. Statistical analysis will be performed using IBM SPSS software (IBM, Armonk, NY, USA). We will compare health gain between groups at baseline and at 6 months, as well as mean pre-operative and post-operative PROM scores between groups. Significance will be denoted at *p* < 0.05, and we will report 95% CIs as appropriate. The statistical test chosen to compare groups will depend on the data distribution and the level of the data (nominal, ordinal or interval/ratio). For parametric data comparing two groups, Student’s *t* test for independent samples will be used. The Welch correction will be used if variances are unequal. If the distributions are not normal or the data ordinal, the Mann-Whitney *U* test will be used. The chi-square test or Fisher’s exact test, depending on observed frequencies, will be used for non-parametric data. Paired tests will be used to compare data within participants pre- and post-surgery as appropriate, with tests (e.g., paired *t* test, Wilcoxon signed-rank test) selected depending on the level and distribution of the data as described above. We recognise that outcomes are likely to be confounded with baseline characteristics (e.g., low physical activity levels, age), type of surgery (TKR/THR) and hospital site, and we will investigate the influence of these baseline confounders on outcomes using multivariable modelling (e.g., logistic regression, analysis of covariance). However, given that this is a feasibility study, and it is therefore not fully powered, such multivariable techniques will be used sparingly and only where justified (e.g., sufficient variable-to-participant ratio). The main aim of inferential analysis of clinical outcomes will be to inform a future fully powered study, rather than to draw direct inferences regarding outcomes.

Using the observed mean and SD of the PROM scores collected from this preliminary data, as well as the reported minimal clinically important difference for the Oxford hip and knee scores and EQ-5D-3 L, a sample size calculation can be performed to inform a larger, future trial. The retention rate derived from these feasibility data will be incorporated into the final sample size to allow for possible attrition. The recruitment rate and resource allocation can also be applied to the final sample size required to plan the future trial requirements. The two NHS trusts involved in this trial carried out almost 4500 hip or knee replacements in 2016. We have chosen to recruit 100 patients for this feasibility trial on the basis of an expected recruitment rate at the two NHS trusts over 2 months.

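### Health gain is compared by unadjusted tests picked from the data, with ANCOVA optional and the baseline PROM score not named; fixing ANCOVA in advance would be a free gain in precision

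*Protocol article*

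**What the plan says.** The Outcomes section states: "The primary clinical outcome measurement for the trial is the effect of vitamin D on health gain following THR/TKR". It defines the measure: "Health gain is calculated as the difference between pre-operative and post-operative PROM scores".

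The Statistical analysis section then says: "We will compare health gain between groups at baseline and at 6 months". The same sentence adds a comparison of mean pre- and post-operative PROM scores. On the choice of test it says: "The statistical test chosen to compare groups will depend on the data distribution and the level of the data". The default is a two-sample test: "For parametric data comparing two groups, Student’s *t* test for independent samples will be used". Welch is used if variances differ. The fallback is a rank test: "If the distributions are not normal or the data ordinal, the Mann-Whitney" test applies. The threshold is: "Significance will be denoted at *p* < 0.05", with 95% CIs as appropriate.

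The section also foresees multivariable modelling, with analysis of covariance as an example. The factors named are baseline characteristics (physical activity and age as examples), type of surgery and hospital site. The limit is that "such multivariable techniques will be used sparingly and only where justified".

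Elsewhere, Baseline assessment says the Oxford and EQ-5D-3L scores will be obtained before surgery, and Randomisation says allocation is 1:1, stratified by site, among patients below 50 nmol/L. The closing paragraph of Statistical analysis says the observed mean and SD of the PROM scores, with a minimal clinically important difference, can be used to size a later trial.

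**The concern.** Three things in the wording fit poorly together.

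- Health gain needs a post-operative score, so there is nothing to compare between groups at baseline.
- The named between-group tests ignore the baseline score, the stratification factor (site) and the type of joint, although the protocol itself expects joint and site to be related to outcome. The model that could use them is optional.
- The choice between a t test and a rank test waits for the data. The Oxford total is a 0 to 48 sum of 12 five-option items, and the protocol does not say whether it counts as ordinal or interval. So it is not settled whether the reported effect will be a mean difference.

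At stake are the width of the confidence interval for the randomised comparison and the usefulness of the variance estimate passed to the definitive trial. Informing that trial is the stated purpose of the inferential analysis.

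**Working it through.** **Inputs.** The only sample-size figure in the protocol is 100 recruits, set from expected recruitment over 2 months. No SD, effect size, power or correlation is given, so there is no precision figure to reproduce. Three inputs are therefore assumed: the correlation r between baseline and 6-month score (0.3, 0.5, 0.7), the SD ratio, and the share of recruits below 50 nmol/L (30 to 60%).

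**1. Definition.** By the Outcomes section, health gain combines a pre- and a post-operative score. At baseline only the first exists. The comparison there cannot be computed.

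**2. Variance with equal SDs (s).**

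- Change score: 2s²(1 − r)
- Post-operative score alone: s²
- ANCOVA on the baseline score: s²(1 − r²)
- ANCOVA / change = (1 + r)/2; ANCOVA / post-operative = 1 − r²

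| r | ANCOVA / change | SE ratio | ANCOVA / post-operative |
|---|---|---|---|
| 0.3 | 0.65 | 0.81 | 0.91 |
| 0.5 | 0.75 | 0.87 | 0.75 |
| 0.7 | 0.85 | 0.92 | 0.51 |

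As an illustration, take an assumed difference of 0.5 SD, two-sided alpha 0.05 and power 0.80. The numbers per arm for r = 0.3 / 0.5 / 0.7 are 88 / 63 / 38 for the change score, 58 / 48 / 33 for ANCOVA, and 63 throughout for the post-operative score alone.

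**3. Small samples.** Randomised patients per arm: 100 × 0.30 / 2 = 15 to 100 × 0.60 / 2 = 30, so N = 30 to 60 in total. Estimating one slope inflates the ANCOVA variance by about 1 + 1/(N − 4), which is 1.038 at N = 30 and 1.018 at N = 60. The ratio to the change score becomes 0.66 to 0.68 (r = 0.3), 0.76 to 0.78 (r = 0.5) and 0.87 to 0.88 (r = 0.7).

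For three covariates (baseline score, joint, site) the same approximation is 1 + 3/(N − 6), which is 1.125 at N = 30. If joint and site explained nothing at all, the ratios would be 0.65 × 1.125 = 0.73, 0.75 × 1.125 = 0.84 and 0.85 × 1.125 = 0.96. The gain shrinks but remains with equal SDs.

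**4. Unequal SDs.** With k = post/pre SD ratio, ANCOVA / change = k²(1 − r²) / (1 + k² − 2rk). For r from 0.3 to 0.7 this is 0.50 to 0.63 at k = 0.8 and 0.87 to 0.998 at k = 1.5. In large samples it does not exceed 1. At N = 30 with three covariates, the least favourable corner is 0.998 × 1.125 = 1.12, a small loss.

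**5. Test selection.** The rule was simulated with no treatment effect: 25 per arm, 6,000 runs, a Shapiro-Wilk test in each arm to trigger Mann-Whitney, and Levene's test to trigger Welch. The protocol does not name these triggers; they are assumed.

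| Data | Rejections | Switched to Mann-Whitney |
|---|---|---|
| Normal | 5.1% | 10% |
| Skewed (gamma, shape 4) | 5.0% | 60% |

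Type I error is kept. What varies is the effect measure that goes with the test.

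**6. The SD carried forward.** If the later trial is analysed by ANCOVA but sized on another SD, its size is multiplied by the inverse ratio, for r = 0.3 to 0.7:

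- change-score SD: 1/0.65 = 1.54 down to 1/0.85 = 1.18
- post-operative SD: 1/0.91 = 1.10 up to 1/0.51 = 1.96

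The protocol does not say which SD is meant, and mentions neither the correlation nor the residual SD.

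**The case against.** The case for leaving the text alone has weight. An unadjusted comparison of change scores between randomised arms is unbiased. The trial is about feasibility, says it is not fully powered, and disclaims direct inference on outcomes. No decision rule hangs on this test. Analysis of covariance, joint and site are all named, and the list of baseline characteristics is open, so the baseline PROM is not excluded. An analysis plan could settle the covariates. Post-operative means are compared as well as change. Patient-level scores will be held, so the correlation can be computed later. All of this stands, and it limits the point to precision and to fixing the effect measure in advance.

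The defence that the baseline phrase is loose wording for comparing scores at each time is plausible, but the same sentence lists those scores separately. The phrase still needs correcting, although no result depends on it.

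Four stronger readings are tempting, and the document does not support them.

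- *The definitive trial would be 1.4 to 1.7 times too large.* That needs the change-score SD and r of 0.2 to 0.4 (1/0.70 = 1.43; 1/0.60 = 1.67). The protocol speaks of the SD of the PROM scores. If that is the post-operative SD, the same r gives 1/(1 − r²) = 1.04 to 1.19.
- *A switch to Mann-Whitney destroys the mean and SD needed for planning.* Both are descriptive statistics, available whichever test is run.
- *Data-driven selection inflates false positives.* The simulation shows it stays near 5%.
- *The plan ignores adjustment.* It foresees it, but as an optional addition.

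**Conclusion.** The point holds as a recommendation to improve the plan, plus one wording error. The main comparison as written is valid but gives up precision that data already being collected could supply, and it leaves open whether the effect will be a mean difference or a rank comparison. With equal SDs and r between 0.3 and 0.7, ANCOVA has 0.65 to 0.85 of the variance of the change score and 0.91 to 0.51 of that of the post-operative score. These ranges rest on assumed correlations and SD ratios. With a larger post-operative SD the gain over the change score can be close to nil, and the statement that ANCOVA is not worse is a large-sample one. The limit to sparing modelling does not justify leaving out the baseline score: with equal SDs the gain survives the degree of freedom spent at 15 to 30 per arm. Severity is moderate to minor.

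**What to change.** In the Statistical analysis section:

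1. Remove the reference to baseline from the comparison of health gain. The comparison of pre-operative PROM scores can stay as a description of the groups.
2. State that the main randomised comparison, supplemented versus unsupplemented among patients below 50 nmol/L, is an ANCOVA of the 6-month score on arm, baseline score of the same instrument, joint (THR or TKR) and site. Report it as an adjusted mean difference with 95% CI whatever the distribution looks like.
3. Keep Mann-Whitney only as a sensitivity analysis for PROM scores.
4. In the closing paragraph on the future sample size, carry forward the residual SD from this model, or the baseline to 6-month correlation alongside the SD, and say which SD is used.

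The cost is a few lines of text and three degrees of freedom for the covariates. No new data are needed, and nothing changes for patients or sites.
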